### Intervention

For the study, post-hospitalization subjects are taken into consideration, after 4 weeks from the hospitalization in the Clinical Unit of Physical Rehabilitation, IRCCS INRCA, in the Ancona and Fermo branches, after having already received the standard treatment. A 10-treatment session is conducted, divided into 2 training sessions per week, for 5 weeks. The control group performs traditional therapy sessions lasting 50 min. The technological intervention group, using Tymo system or Walker View, carries out 30 min of traditional therapy and 20 min of treatment with a robotic system. Cardiac activity monitoring is planned during robotic treatments in order to detect the heart rate during physical activity [32].

Individual participants must complete at least 80% of the sessions. Recovery of 2 sessions will be possible.

All patients included in the study perform traditional rehabilitation treatments, consisting in:
Breathing, relaxation and postural harmonization exercises;Exercises of active mobility and stretching;Eye-hand coordination exercises and couple exercises;Exercises for walking and verticalization.

The robotic treatment consists of using two different devices: Tymo system or Walker view.

Tymo system is a wireless platform for the balance and the postural control training. Tymo system is connected to a screen and provides virtual reality games, adaptable to the functional capacity of the patient. Through the games proposed, the physiotherapist decides to work in a dimension (antero-posterior or medio-lateral dimension) or in two dimensions (combining the antero-posterior and medio-lateral movements).

Walker view is a treadmill equipped with a sensorized belt with eight load cells and a 3D camera to detect length, speed and symmetry of the pace and load, range of the trunk, hips and knees. Patients are asked to walk at a comfortable speed, while the physiotherapist is able to work on different parameters such as step length, load distribution, and step height. The setting takes place taking into account the clinical conditions of each patient, customizing the intervention. The Walker View offers visual and auditory feedback to the patient, so as to correct gait in real time.

Adverse events, although unlikely, could be related to the use of technology such as falls and/or pain at knees or ankles.

### Outcomes

All outcome measures follow a standardized operating procedure. Table 1 shows the primary outcome and the secondary outcomes with the expected result at the end of the treatment. The expected improvement was derived from the analysis of similar studies [29], collected for the evaluation of the sample size for each outcomes.

**Table 1 Tab1:** Outcomes and clinical assessments

Outcome(s)	Clinical assessment	Expected improvement at the end of treatment
Primary: Improvement of the overall mobility (balance + walking ability)	POMA	10%
Secondary: Improvement of gait speed	Instrumental Gait analysis	12%
Secondary: Decrease of fear of falling	FES-I Short form	15%

*POMA* Performance-Oriented Mobility Assessment, *FES-I* Short Falls Efficacy Scale – International

Further evaluations are carried out as follows:
Length and asymmetry of the step, through instrumental Gait Analysis;Walking and functional status through the Functional Ambulation Category and Barthel Index scale;Acceptance of the technology, through Psychosocial impact of assisted device scale (PIADS) questionnaireQuality of life, through SF-12 questionnaire.

#### Mini-mental state examination (MMSE)

The Mini-Mental State Examination was designed as a clinical method for grading cognitive impairment. The score ranges from 0 to 30: scores ≥24 indicate normality, between 18 and 23 indicate mild cognitive impairment, between 11 and 17 average cognitive deficits, scores ≤10 severe cognitive impairment. The reported score is corrected for age and education [33].

#### Rankin scale (RA)

It is a simple scale for the evaluation of the outcomes following the stroke. Reliability is well defined. The individual categories are essentially based on patient mobility. There are 6 grades of classification from 0 to 5, where 0 means independence [34].

#### Hoehn and Yahr scale (SHY)

This scale is used in the medical field to describe the symptoms of Parkinson’s disease progression. It was originally published in 1967 in the Neurology Journal by Melvin Yahr and Margaret Hoehn, and included stages 1 to 5. Since then, a modified scale has been proposed, with the addition of stages 1.5 and 2.5 describing the intermediate course of the disease [35].

#### Barthel index (BI)

BI is an ordinal scale used to measure a subject’s performance in everyday life activities. The index analyzes ten variables that describe the activities of daily life and mobility. Each item is assigned a score between 0 and 10 depending on the degree of patient’s functionality: full, reduced or no functionality. A high overall score is associated with a greater probability of being able to live at home independently after discharge from the hospital [36].

#### Functional ambulation categories (FAC)

The scale is used to classify the severity level of gait disturbances in neurological disorders. It provides a hierarchical classification from level 0 (impossible walking) to level 5 (no limitation) [37].

#### SF-12 health survey (SF-12)

The SF-12 questionnaire was originally developed in the United States to provide a short alternative form to the SF-36 questionnaire. The SF-12 is composed of 12 items that produce two measurements related to two different aspects of health: physical health and mental health. The subject is asked to answer on how he feels and how he is able to carry out the usual activities, evaluating the current day and the 4 previous weeks [38].

#### Tinetti’s scale or performance-oriented mobility assessment (POMA)

The Tinetti scale is a tool used to evaluate balance and gait performance. The test is used clinically to determine the mobility status of a subject or to assess changes in balance and gait time. The total POMA (POMA-T) consists of two sub-scales: the balance evaluation scale (“balance scale” or POMA-B) and the gait evaluation scale (“gait scale” or POMA-G). the maximum score is 28 points: in detail, the maximum score of the POMA-B is 16, while for the POMA-G the maximum score is 12 [27].

#### Short falls efficacy scale - international (FES-I- short)

The scale measures the “fear of falling”. The scale can be self-administered or administered during the interview. The cut offs for the fear of falling are divided as follows: a score between 7 and 8 indicates a low concern, between 9 and 12 a moderate concern and between 14 and 28, high concern [39].

#### Psychosocial impact of assistive devices scale (PIADS)

It is a self-completed questionnaire by the user and it assesses the impact that the device has on the person. Through 26 questions it tries to detect how the device has brought about a perception of change with respect to one’s availability for new experiences (6 questions), skills (ability to cope with daily activities and challenges - 12 questions) and self-esteem (security and self-confidence - 8 questions). Every question is answered on a visual scale marked by − 3 (the device has strongly limited my independence) to + 3 (the device has greatly improved my independence) [40].

#### Assistive device predisposition assessment (ATDPA)

The purpose of the tool is to assess user expectations about technological devices [41].

#### Geriatric depression scale 5-items version (GDS)

This questionnaire assesses the current condition of the patient’s mood. For the screening required by our study, only the first five items of the scale can be used. The answers highlighted indicate the statements expected by a non-depressed subject [42].

#### Clinical dementia rating scale (CDR)

This questionnaire assesses the patient’s dementia status. The CDR is a 5-point scale used to characterize six domains: memory, orientation, judgment and problem solving, business, home and hobby and personal care [43].

#### Gait analysis and instrumental postural analysis

Gait analysis is the systematic study of human locomotion, augmented by instrumentation for measuring body movements, body mechanics, and the activity of the muscles [44]. Gait analysis is performed on the selected patients at the Gait Analysis Laboratory in the Department of Physical Rehabilitation at branch of IRCSS INRCA Ancona. Instrumented gait analysis is performed using BTS GAITLAB (BTS Bioengineering, Italy) system with six infrared cameras (100 Hz) and 2 force plates (50 Hz). The system is used to acquire both kinematic and kinetic data. Three-dimensional kinematic data are recorded with the help of 22 reflective infrared markers using Helen Hayes protocol [45]. The floor-mounted force plates are used to acquire the kinetic data. The subjects walk at a self-selected speed. The instrumental postural analysis studies the complex control system that must keep the center of gravity constantly in a balanced position. This analysis is carried out through an advanced system consisting composed by a camera for video recording and a platform with 2 triaxial sensory plates (Podium, BTS Bioengineering, Italy). With this system, it is possible to simultaneously visualize the three components of force: vertical, antero-posterior and lateral. It allows to evaluate, in augmented reality, the symmetry of the load and the trend of the pressure center.

A summary of all data collected and when these are collected is provided ion Table 2.

**Table 2 Tab2:** Schedule of assessment and outcome measures

Outcome	Clinical assessment	R	T1	FW1	FW2	FW3
Cognitive State	Mini Mental State Examination	✓				
Gait parameters	Functional Ambulation Category	✓	✓	✓	✓	✓
Disability State	Rankin Scale	✓				
Cognitive State	CDR	✓				
Functional State	Barthel Index	✓	✓	✓	✓	✓
Parkinson State	Hoehn and Yahr Scale	✓				
Quality of life	SF-12 Health Survey	✓	✓	✓	✓	✓
Sociodemographic characteristics	Check-list	✓				
Motor ability	Motricity index	✓	✓	✓	✓	✓
Depression State	Geriatric Depression scale 5-items version	✓				
Attitude to technology	Assistive Device Predisposition Assessment – Scala E	✓				
Fall risk	Scala di Tinetti	✓	✓	✓	✓	✓
Gait parameters	Gait Analysis + instrumental postural analysis	✓	✓	✓	✓	✓
Fear of falling	Short Falls Efficacy Scale - International	✓	✓	✓	✓	✓
Acceptance of technology	Psychosocial impact of assisted device scale - PIADS		✓			

*R* Recruitment, *T1* end of treatment, *FW1* first follow up at 6 months since the end of treatment, *FW2* second follow up at 1 year since the end of treatment, *FW3* third follow up at 2 years since the end of treatment

### Data management

Personal data collected during the trial will be handled and stored in accordance with the General Data Protection Regulation (GDPR) 2018. Use of the study data will be controlled by the principal investigator. All data and documentation related to the trial will be stored in accordance with applicable regulatory requirements and access to data will be restricted to authorized trial personnel.

### Data analysis

Continuous variables will be reported as either mean and standard deviation (SD) or median and interquartile range (IQR) on the basis of their distribution (assessed using Shapiro-Wilk test). Comparison of variables between groups will be performed by unpaired Student t test or Mann-Whitney U test according to their distribution. Categorical variables will be expressed as absolute number and percentage and statistical significance will be assessed by Chi-square test or Fisher Exact.

In a second step, the analysis of the follow-up data will be carried out in order to evaluate the effectiveness of the intervention. This analysis phase will involve the use of multivariate statistical techniques, in particular repeated measures analysis of variance (ANOVA), in order to compare the changes over time in the outcome measures between the intervention group and the control group. The statistical significant will be set at *p* < 0.05.

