### Sample size

The Performance-Oriented Mobility Assessment (POMA) [27], a test widely used to assess walking ability and associated with equilibrium, is used to calculate the sample size [28]. Assuming a small effect size of 10% [29], it is estimated that the overall sample size needed to capture this effect size is of 153 subjects, assuming a statistical power of 80%, a significance level of 0.05, three groups and 5 repeated assessments (a baseline and 4 follow-ups) in an ANOVA model within-between interactions. Even assuming a 25% drop out rate, the total number required would be 195 subjects (65 for each arm).

It is hypothesized that this sample dimension is more than sufficient to grasp a variation also for secondary outcomes for which a treatment effect size is assumed of a similar or higher entity than that identified for the primary outcome [30, 31].

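### Repeated measures ANOVA over five visits by default uses only patients with complete data, so at 25% drop-out it can discard end-of-treatment POMA values that a mixed model would keep

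*Protocol article*

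**What the plan says.** The Data analysis section of the protocol names the effectiveness method as "in particular repeated measures analysis of variance (ANOVA), in order to compare the changes over time in the outcome measures". The comparison is of the intervention group with the control group.

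The Sample size section uses the same model and tests the interaction of arm with visit: "assuming a statistical power of 80%, a significance level of 0.05, three groups and 5 repeated assessments (a baseline and 4 follow-ups". Baseline is therefore one of the five responses. The section arrives at 153 patients and then raises this to 195, 65 per arm: "Even assuming a 25% drop out rate".

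The primary aim (Study aims and objective) covers POMA at end of treatment, 6 months, 1 year and 2 years. Table 1 in Outcomes gives the expected POMA improvement, 10%, at end of treatment. The protocol does not say when or why patients are expected to leave, what correlation between visits was assumed, or how an incomplete patient enters the ANOVA.

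**The concern.** Repeated measures ANOVA works on complete rows, in both its univariate and its multivariate form. Left at its default, it removes a patient who has baseline and end-of-treatment POMA but misses the 2-year visit, and removes that patient from every visit. The expected benefit is stated for a visit about 5 weeks after the start, while the rows must run to about 25 months. Early data that were collected would go unused because later data are missing.

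Precision at end of treatment would be lower than it need be. If those who leave differ from those who stay, and differ in another way in another arm, the completers no longer compare like with like. Two further features of the named method matter separately: it takes baseline as a response without using it for adjustment, and its univariate interaction test assumes sphericity.

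**Working it through.** **Inputs from the protocol.** Three arms, five visits, significance level 0.05, power 80%, 153 before and 195 after 25% drop-out (Sample size); visits at baseline, end of treatment (5 weeks), and 6, 12 and 24 months later.

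**Assumed, because not stated.** The 10% effect size read as Cohen's f = 0.10; correlation between visits rho; sphericity factor epsilon; drop-out timing and mechanism.

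**1. The plan's own figure.** For the within-between interaction:

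- lambda = f² × N × m × epsilon / (1 − rho)
- df1 = (k − 1)(m − 1) × epsilon; df2 = (N − k)(m − 1) × epsilon

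With f = 0.10, N = 153, k = 3, m = 5, rho = 0.5, epsilon = 1: lambda = 0.01 × 153 × 5 / 0.5 = 15.3, df1 = 8, df2 = 600, power 0.803. N = 152 gives 0.799, so 153 is reproduced. On a grid of rho (0.3, 0.5, 0.6, 0.7, 0.8) by epsilon (1, 0.8, 0.75, 0.6, 0.5), only rho 0.5 with epsilon 1 gives 153.

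**2. Patients left.** 195 × 0.75 = 146.25, so about 146 complete rows (49 per arm). On the inputs of step 1, interaction power is then 0.78.

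**3. Standard error at end of treatment, missing-data part only.** Completer SE divided by all-available SE = √(patients seen at end of treatment / 146).

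| When the 25% leave | Seen at end of treatment | SE ratio |
|---|---|---|
| All after end of treatment | 195 | 1/√0.75 = 1.155 |
| Half before, half after | 195 × 0.875 ≈ 171 | √(171/146) ≈ 1.08 |
| All before | 146 | 1.00 |

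In the first row, at an illustrative pairwise difference of 0.5 SD, power is 0.81 with 65 per arm and 0.70 with 49.

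**4. Baseline adjustment, a separate gain.** In SD² units the variance of a change score is 2(1 − rho), and after baseline adjustment it is 1 − rho². The ratio is (1 + rho)/2: 0.75 at rho = 0.5 (25% lower) and 0.90 at rho = 0.8 (10% lower). This has nothing to do with missing data.

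**5. Bias at end of treatment, by simulation** (4,000 trials per scenario, 65 per arm, patients leaving after end of treatment).

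True difference 0.5 SD, serial correlation 0.8, drop-out 25% to 28%:

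| Drop-out mechanism | All available | Completers |
|---|---|---|
| Completely random | 0.504 | 0.504 |
| Depends on the end-of-treatment score, alike in both arms | 0.498 | 0.484 |
| Depends on that score in the control arm only | 0.499 | 0.454 |

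The shortfall is nil, 0.498 − 0.484 = 0.014 SD (about 3%), and 0.499 − 0.454 = 0.045 SD (about 9%).

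A harsher set has no true effect, equal correlation 0.5, and drop-out of 35% in control and 20% in each device arm, which averages (35 + 20 + 20)/3 = 25%. Poor responders are more likely to leave (logistic slopes 0.5 and 1.0). Completer bias is −0.073 and −0.121 SD; the all-available estimate is unbiased.

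**6. Sphericity, the secondary point.** Type I error of the uncorrected univariate interaction test, 20,000 null trials, N = 153: 0.050 under equal correlation; 0.064, 0.075 and 0.086 under first-order autoregressive correlation of 0.5, 0.7 and 0.9; 0.093 with exponential decay over the actual months. Epsilon for the three autoregressive cases is 0.81, 0.69 and 0.58. Smaller runs gave 0.055 to 0.094 over the same autoregressive range.

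**The case against.** The protocol does not say that incomplete patients are dropped, nor that the F test is uncorrected. Both are defaults of the method. Rules for missing data, analysis sets and epsilon corrections commonly sit in an analysis plan or full protocol, neither of which is shown, and this article is condensed. That stands as a limit on wording. It does not remove the point, because the method itself is stated, and both its forms need complete rows before any further rule is applied.

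Four stronger readings are tempting, and the document does not support them.

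- **That the end-of-treatment result is biased.** No drop-out mechanism is given. Informative attrition is plausible: only outcome assessors are blinded, and Participants excludes life expectancy under 1 year while follow-up runs to 2 years. Plausible is as far as it goes.
- **That the variance would fall by about 43%.** That multiplies two separate gains (0.75 × 0.75 ≈ 0.56). It needs every drop-out to leave after end of treatment and a correlation of 0.5, and neither is stated.
- **That the F test fails to hold 5%.** This depends on decaying correlations and on no correction. Data analysis speaks of multivariate techniques; the multivariate form needs no sphericity, though it still needs complete rows. Nor does sphericity bias the end-of-treatment estimate.
- **That the session rule removes patients from analysis.** "Individual participants must complete at least 80% of the sessions" sets an adherence requirement; nothing in Intervention or Data analysis says that patients below it are excluded from the analysis.

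Two further objections are fair. End of treatment is one of four visits in the primary aim and is not declared the sole primary contrast. Treating baseline as a response is also a recognised choice, and loses nothing if the arms share a common baseline mean; classical repeated measures ANOVA does not impose that.

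**Conclusion.** The point holds as an avoidable loss of information, with a conditional risk of bias. At the plan's own 25% drop-out, the named method by default keeps about 146 of 195 patients.

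- **Missing data:** 0% to about 15% on the standard error at end of treatment, according to when patients leave.
- **Baseline adjustment:** 25% lower variance at an assumed correlation of 0.5, 10% at 0.8. This gain is available even with no drop-out.
- **Bias:** nil under random drop-out, about 0.01 SD when score-related drop-out is alike in the arms, and about 0.05 to 0.12 SD in assumed scenarios where it differs by arm.
- **Type I error:** roughly 6% to 10% for an uncorrected univariate interaction test under assumed decaying correlations. This falls away if a correction or the multivariate form is used.

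The count of 146 and the upper limit on the standard error follow from the protocol's figures and the method's default. The remaining sizes rest on correlations and drop-out patterns that the protocol does not give.

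**What to change.** In Data analysis, replace repeated measures ANOVA with a likelihood-based mixed model for repeated measures:

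- all randomised patients, in their assigned arm;
- all available follow-up POMA values as responses (end of treatment, 6 months, 1 year, 2 years);
- arm, visit, arm-by-visit, baseline POMA and baseline-by-visit as fixed effects;
- unstructured covariance, so that sphericity is not assumed;
- explicit contrasts of each device with control at each visit, including end of treatment.

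The model is valid when missingness depends only on observed data. It uses early values from patients who leave later; it does not repair drop-out that depends on unobserved values. A missing-not-at-random analysis is optional. Repeated measures ANOVA on completers can stay as a sensitivity analysis.

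The cost is a change of analysis wording and slightly more modelling work. No new data or visits are needed.

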## Methods/design

### Trial design

This study is a single blinded (outcome assessors) randomized controlled trial. One hundred ninety-five patients with PD will be recruited and randomly divided into three groups, to receive a traditional rehabilitation program or, in addition to the traditional therapy, a robotic rehabilitation using Tymo system or Walker View. Assessments will be performed at baseline, at the end of treatment and 6 months, 1 year and 2 years from the end of the treatment. For the duration of the study, patients cannot receive treatments through robotic devices but will continue to be followed as outpatients by our rehabilitation department.

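### Baseline POMA is analysed as one of five responses; adjusting for it as a covariate would be more precise, by an amount that depends on the correlation and on the time course of the effect

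*Protocol article*

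**What the plan says.** The Sample size section of the protocol article bases the trial on "three groups and 5 repeated assessments (a baseline and 4 follow-ups) in an ANOVA model within-between interactions", "assuming a statistical power of 80%, a significance level of 0.05", and concludes that "the overall sample size needed to capture this effect size is of 153 subjects". The Data analysis section plans "repeated measures analysis of variance (ANOVA), in order to compare the changes over time in the outcome measures" between the intervention and control groups, and names no baseline covariate. The Trial design section sets the visits: "Assessments will be performed at baseline, at the end of treatment and 6 months, 1 year and 2 years from the end of the treatment".

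Table 2 schedules POMA (listed there as the Tinetti scale), gait analysis and the short FES-I at recruitment and at all four later visits, so each of these outcomes has its own baseline value. Table 1 gives an expected improvement for POMA at end of treatment only (10%). No SD, no correlation between assessments and no later time course are stated.

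**The concern.** With baseline as a level of the time factor, the treatment effect is read from the group-by-time interaction, that is, from differences in change. In a randomised trial the arms have the same expected baseline, so the baseline value carries no treatment effect. Used as a response, it adds its own error to the contrasts between baseline and follow-up. Used as a covariate, it removes variance from the follow-up values instead.

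The loss is present with complete data and perfect sphericity, so it is separate from missed visits and from departures from sphericity. What is at stake is precision on the primary outcome, in a trial sized at 80% power.

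**Working it through.** **Inputs.** From the Sample size section: effect size 10%, read as Cohen's f = 0.10; 3 groups; 5 assessments; alpha 0.05; N = 153. Assumed, because the documents do not say: compound symmetry with correlation ρ, equal effect of the two devices, equal allocation among those analysed, and the time course.

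**1. Reproduce the plan's N.** For the within-between interaction, λ = f²·N·m/(1−ρ), with (3−1)(5−1) = 8 and (N−3)·4 df.
- ρ = 0.5: λ = 0.01·153·5/0.5 = 15.3; df 8 and 600; power 0.803. N = 153 is reproduced.
- ρ = 0.4 gives N = 183 and ρ = 0.6 gives 123. Four assessments at ρ = 0.5 give 173.

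So the stated N implies ρ = 0.5 with baseline counted as the fifth response.

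**2. Express f as a device-control difference.** One third of patients are controls and two thirds receive a device, so the between-arm variance of the effect is (2/9)d². A sustained profile 0, 1, 1, 1, 1 has variance 0.8·0.2 = 0.16 over the five times. Setting (2/9)·0.16·d² = 0.01 gives d² = 0.281 and d = 0.53 SD. Let g = N·(2/9)·d² = 153·0.0625 = 9.56.

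**3. One visit (2 df).** Error variance is 2(1−ρ) for change from baseline and 1−ρ² with baseline as covariate.
- At ρ = 0.5 these are 1.00 and 0.75, a 25% reduction; 1/0.75 = 1.33, equivalent to one third more patients.
- Change: λ = 9.56/1.00 = 9.56, power 0.79.
- Covariate: λ = 9.56/0.75 = 12.75, power 0.90.

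**4. Like for like over all follow-ups (8 df).** Let S1 and S2 be the sum and the sum of squares of the follow-up effects, in units of d. Then λ = g·Q/(1−ρ), with
- planned interaction: Q = S2 − S1²/5
- joint test of arm differences at the four follow-ups given baseline: Q = S2 − ρ·S1²/(1+4ρ)

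Since ρ/(1+4ρ) is below 1/5 for any ρ from 0 up to but not including 1, the second Q is never smaller. At ρ = 0.5 and N = 153:

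| Effect at T1, FW1, FW2, FW3 | Q planned | Q adjusted | λ planned | λ adjusted | Power planned | Power adjusted |
|---|---|---|---|---|---|---|
| Sustained: 1, 1, 1, 1 | 0.800 | 1.333 | 15.3 | 25.5 | 0.80 | 0.97 |
| Fading: 1, 0.75, 0.5, 0.25 (or growing, reversed) | 0.625 | 0.833 | 11.95 | 15.94 | 0.68 | 0.82 |
| End of treatment only: 1, 0, 0, 0 | 0.800 | 0.833 | 15.3 | 15.94 | 0.80 | 0.82 |

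**5. Other correlations, d held at 0.53.**
- ρ = 0.3: variance at one visit 1.40 against 0.91; 2-df power at end of treatment 0.63 against 0.83.
- ρ = 0.7: variance 0.60 against 0.51 (15% less); 2-df power 0.95 against 0.98. The planned interaction itself has 0.97 for a sustained effect.

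**6. The tested term matters.** If baseline becomes a covariate but arm-by-visit over the four follow-ups stays the test (6 df), then Q = S2 − S1²/4. For a sustained effect this is 4 − 16/4 = 0, so power is 0.05. For the fading profile it is 0.3125 and power is about 0.40.

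**7. After dropout.** With 25% of 195 lost, 195·0.75 leaves about 146. At ρ = 0.5 and a sustained effect, the planned interaction has 0.78 and the adjusted joint test 0.96.

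**The case against.** A reader might infer that the plan has 80% power where the same patients would give 90%. The documents do not support that as an unconditional statement. The 0.80 belongs to an 8-df interaction over five times and the 0.90 to a 2-df test at end of treatment, which is a different hypothesis. The stated primary aim covers all four follow-ups. Compared like for like, the gain at ρ = 0.5 runs from 0.02 to 0.17 in the three patterns of step 4, and it would be nil if the follow-up effects summed to zero. This part of the objection stands.

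The end-of-treatment test also keeps its 0.90 only where the full effect is present at that visit. For an effect growing as 0.25, 0.5, 0.75, 1 its power is 0.11, and for one that starts at 6 months it is 0.05; the planned test has 0.68 and 0.95. This also stands: choosing one visit has a price.

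The correlation of 0.5 is inferred from N and may not hold for POMA. Nor does baseline error enter every part of the interaction, because contrasts among the four follow-ups do not use it. Both points limit the size of the gain, not its direction.

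Finally, repeated measures ANOVA with baseline as a level is a valid test, the two sections agree with each other, and covariates are often left to an analysis plan that is not shown here. The first two points are right, so this is neither an error of validity nor a contradiction. The third does not dispose of the matter: the article itself states the model and derives its N from it with baseline as a fifth response.

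**Conclusion.** The point holds as a loss of efficiency in a valid analysis, and a change is worth making. Under randomisation and compound symmetry, adjusting for baseline is never less precise for the same comparison. At ρ = 0.5, d = 0.53 SD and equally effective devices, it removes 25% of the error variance at a single visit. In the three time courses tabulated it raises 8-df power by 0.17, 0.14 or 0.02. The gain is larger at ρ = 0.3 and small at ρ = 0.7. It is realised only if the tested term is changed together with the role of baseline. The documents do not support reading this as an invalid test or as a fixed gain of ten percentage points.

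**What to change.** In Data analysis, state that the responses are POMA at T1, FW1, FW2 and FW3, and that the model contains arm, visit, arm-by-visit, baseline POMA and baseline-by-visit. Name the primary test as the baseline-adjusted arm difference, in one of two forms:
- jointly over the four follow-ups (8 df), which matches the stated primary aim; or
- at one visit named in advance, such as end of treatment, the only time for which Table 1 gives an expected improvement.

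Say explicitly that the 6-df arm-by-visit interaction among the follow-ups is not the primary test. Report the adjusted difference of each device from control with its confidence interval. Treat gait speed and the short FES-I in the same way, each with its own baseline. In Sample size, describe the power for the test chosen and state the assumed correlation and time course.

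The cost is wording, with no new data and no extra patients. The baseline terms use four degrees of freedom (one slope per visit). If one visit is chosen, the primary test has no sensitivity to effects that appear only later. Data collection is reported as ongoing, so the change should be fixed before outcome data are analysed.
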